**Trial registration number::**

NCT02575599.

Strengths and limitations of this studyUse of a complex intervention design.Developing a theory-based Guided Self-Determination programme for adults with type 2 diabetes (T2DM).Testing a web-based intervention in general practice in order to increase self-management among adults with T2DM.The assignment of patients to the intervention and control groups will not be random.The quasi-experimental design requires cautiousness about drawing inferences and conclusions from the data.

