Diabetes-specific distress will be assessed using the 17-item version of the Diabetes Distress Scale (DDS).^53^ The DDS has four subscales: emotional burden (five items), physician-related distress (four items), regimen distress (five items) and diabetes-related interpersonal distress (three items). The responses are on a scale (1–6) from ‘not a problem’ to ‘a very serious problem’. The scale has been validated in a previous Norwegian study.^54^

In addition, clinical parameter, such as HbA1c, will be measured by a blood sample at the GP office at baseline and at the end of the intervention. Self-reported height and weight (for body mass index calculating) and medical treatment will be collected as well. The accessibility and practice of the web-based portal will be measured by asking participants to write down the number of log-ons, time spent on filling the reflection sheets, time spent on e-consultations and the number of feedbacks from the nurses.

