#### Recruitment and data collection

The study will be carried out in general practices in the western part of Norway. To accomplish the requirement of trained GSD nurses, trained nurses working in general practices will conduct the GSD intervention. Participants with T2DM to be assigned to the intervention group will therefore be recruited from the practices where the nurses are working. Participants assigned to the control group will be recruited from other general practices with employed registered nurses without the GSD training. They will continue with their regular consultations in general practice. Inclusion and exclusion criteria are the same as described for the feasibility study.

All patients considered eligible for the study will be invited by mail to participate. Those who agree to participate and return a written informed consent will be enrolled and the nurse at each selected general practice will then make an appointment with the patient to start the GSD intervention.

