#### Outcome assessments

Measurements are scheduled at three time points: at baseline, 12–16 weeks later at the end of the intervention and 6 months after finishing the intervention.

The patient-reported outcome measures to be collected during this evaluation study will be finalised during the feasibility study, but are likely to be the same as described in the feasibility study. Regarding the goal attainment measure, we expect that the intervention group will report having more goals, more ambitious goals and more progress towards attaining their goals. Other hypothesised benefits of the intervention include increases in PAM scores on patient activation, HCCQ scores on autonomy support, PCD scores on competence, TSRQ scores on autonomy and control, SE-type 2 scores on self-efficacy, SDSCA scores on self-care activities, WHO-5 scores on emotional well-being and decrease in DDS scores on diabetes distress. Clinical outcomes described in the feasibility study (ie, HbA1c) will also be collected at all three time points. We predict reductions in these outcomes relative to the control group.

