#### Data analysis

The quantitative data will be analysed using SPSS V.22 (IBM Corp, Armonk, New York, USA). Descriptive statistical analyses will include frequencies, means, SDs and CIs. The effect of the intervention on outcomes will be analysed by regression analyses with the following covariates: baseline scores, age and gender.

A supplementary analysis will assess whether patient-determined goals predict change on outcomes, that is, whether patients' change goals for particular self-care activities or psychological outcomes predict greater improvements on those outcomes (eg, for analysis of frequency of blood glucose self-monitoring, we will assess the potential impact of each patient's goal, if any, for blood glucose self-monitoring). We will also explore the possibility of pooling outcome results according to whether a patient had a goal to improve that outcome, for example, estimating the pooled effect size for change in each patient's primary chosen goal.

Additional analyses will assess patient usage of and satisfaction with the intervention tools, as well as facilitators and barriers to adoption of the web-based GSD, including the quality of the communication via secure messages with the nurses. We will also examine the nurses' perceived facilitators and barriers to the adoption of the web-based GSD.

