Possible limitations, especially those related to our evaluation study in the third phase, include the fact that assignment of patients to the intervention and control groups will not be random. This sampling, therefore, requires cautiousness about drawing inferences and conclusions from the data. In addition, the power of the study to assess improvement on any single outcome is reduced by the fact that only a subset of patients will have any particular outcome as a goal of their participation. In effect, the evaluation study can be thought of as a set of substudies, one for each outcome. However, our analyses will be designed to compensate for this departure from the top-down, researcher-driven design used in traditional non-personalised interventions. Finally, long-term (ie, > 6 months) effects of the web-based GSD intervention will not be assessed in this study. However, if this intervention is judged effective in the current study, this should provide the information necessary to conduct a definitive study of its long-term effects.

To the best of our knowledge, this will be the first study examining the GSD intervention adapted to a web-based version for adults with T2DM in general practice. We therefore expect that the results of this study will add significantly to the body of knowledge regarding web-based interventions for improving self-management among people with T2DM.

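### The Phase 3 models for PAM and the other non-HbA1c outcomes leave out baseline HbA1c, although groups are formed by practice and HbA1c is measured at Phase 3 baseline

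*Protocol article*

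**What the plan says.** The Data analysis section of the evaluation study (Phase 3) gives the whole effect model in one sentence, as regression "with the following covariates: baseline scores, age and gender". No matching, propensity score or further adjustment is mentioned.

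The Recruitment and data collection section shows how the groups arise. For the intervention: "Participants with T2DM to be assigned to the intervention group will therefore be recruited from the practices where the nurses are working". For the controls: "Participants assigned to the control group will be recruited from other general practices with employed registered nurses without the GSD training". Patients in both groups are invited by mail and enter if they consent. The limitations in the Discussion concede that "assignment of patients to the intervention and control groups will not be random" and ask for caution in drawing conclusions.

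On available data, the Phase 3 Outcome assessments section says: "Clinical outcomes described in the feasibility study (ie, HbA1c) will also be collected at all three time points". The first of these time points is baseline. The same section says that the patient-reported measures are still to be finalised but will probably match those of the feasibility study. BMI and treatment are named only in the Phase 2 Secondary outcomes section: "Self-reported height and weight (for body mass index calculating) and medical treatment will be collected as well". Disease duration appears only as an eligibility threshold of more than 3 months. The Sample size calculation section makes change in PAM the primary endpoint.

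**The concern.** Group membership depends on which practice a patient attends and on whether the patient answers the invitation. Glycaemic control, treatment and other features of case mix may therefore differ between groups. Covariate adjustment is the only analytic protection against this that the article states. For PAM it consists of baseline PAM, age and gender, with no measure of disease severity, although one is measured at the same baseline.

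If patients in one set of practices have poorer control at entry, and control is related to later activation beyond what baseline activation explains, part of the difference between practices would be reported as an effect of GSD. The same applies to self-care, distress, well-being and the other questionnaire outcomes.

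**Working it through.** **1. The plan's own figure.** Inputs from the Sample size calculation section: difference 6 points, SD 11.1, power 90%, significance level 5% (taken as two-sided).

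n per group = 2 × (1.960 + 1.282)² × 11.1² / 6² = 71.9, so 72. This reproduces the stated 72, and the point does not rest on a wrong sample size.

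**2. Which models lack what.** With baseline scores read as each outcome's own baseline:

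| Model | Baseline HbA1c | Baseline PAM | Treatment, BMI |
|---|---|---|---|
| PAM (primary) | absent | present | absent |
| Other questionnaires | absent | absent | absent |
| HbA1c | present | absent | absent |

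Collection at Phase 3 baseline is explicit for HbA1c. It is implied for PAM as the primary endpoint. It is not stated for treatment and BMI.

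**3. Illustrative bias on PAM.** Bias = r × d × SD. Here r is the SDs of PAM per SD of the omitted covariate, given baseline PAM, age and gender, and d is the imbalance between groups in SD units. SD = 11.1 is from the article; r and d are assumptions. Entries are PAM points:

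| r | d = 0.1 | d = 0.2 | d = 0.3 | d = 0.5 |
|---|---|---|---|---|
| 0.05 | 0.06 | 0.11 | 0.17 | 0.28 |
| 0.1 | 0.11 | 0.22 | 0.33 | 0.56 |
| 0.2 | 0.22 | 0.44 | 0.67 | 1.11 |
| 0.3 | 0.33 | 0.67 | 1.00 | 1.66 |

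The range of 0.06 to 1.66 points is about 1% to 28% of the 6-point target. With d = 0 the bias is zero.

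**4. Residual SD.** If r is read as a partial correlation, the SD left after baseline adjustment is the right multiplier. For an assumed baseline-to-follow-up correlation of 0.5 to 0.7:

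- 11.1 × √(1 − 0.5²) = 9.6
- 11.1 × √(1 − 0.7²) = 7.9

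The table entries then fall by 13% to 29%. The largest becomes 0.3 × 0.5 × 9.6 = 1.44 or 0.3 × 0.5 × 7.9 = 1.19 points.

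**5. What this does to the test.** With 20% loss from 86, about 69 per group remain, and SE = 11.1 × √(2/69) = 1.89. Under a normal approximation, a bias of 0.22 points gives a type I error of 5.2%, and 1.0 point gives 8.3%. Three covariates in the same direction at r = 0.1 and d = 0.3 also give 3 × 0.1 × 0.3 × 11.1 = 1.0 point.

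**6. Cost.** Evaluable patients: 172 × 0.8 = 137.6, about 138. HbA1c and BMI use one degree of freedom each. Treatment in three categories (an assumed coding) uses two. That is four in all.

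**The case against.** The strongest reply is that the plan already adjusts for the most important covariate. Baseline PAM removes whatever confounding acts through baseline activation, and only imbalance remaining after that counts. This stands, and it is why the lower part of the range deserves as much weight as the upper.

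The size is also pure assumption: no passage gives an association or an imbalance. This stands too.

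A reader might infer that baseline HbA1c is missing from every model and that the HbA1c result is the most exposed. The article does not support this, since the HbA1c model contains its own baseline. A reader might also infer that treatment, BMI and disease duration are already recorded in Phase 3. The article names treatment and BMI only for the feasibility phase, and the Phase 3 carry-over of clinical outcomes names HbA1c alone. Duration is given only as a threshold.

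Two further defences are weaker. Baseline scores could be read as all baseline questionnaire scores in every model, but HbA1c is a laboratory value, and if that broad reading is meant the wording should say so. The Discussion's promise that the analyses will compensate concerns patient-chosen goals, not allocation. Nor is the covariate list a detail left to an analysis plan: the article states it. By contrast, the absence of balance tables and propensity methods may be condensation and is not held against it.

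**Conclusion.** The point holds in a limited form. For the primary endpoint and the other non-HbA1c outcomes, a non-randomised comparison between practices is adjusted by a short fixed list that omits baseline HbA1c, which Phase 3 measures. That leaves confounding that could be reduced at almost no cost. The size is unknown. The illustrative shift of up to about 1.7 PAM points per omitted covariate assumes r up to 0.3, d up to 0.5 SD and the full SD of 11.1. It is smaller with the residual SD and zero under balance.

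It would go too far to conclude that the planned estimate is materially biased, or that a longer list would make the groups comparable. Practice and nurse coincide with group, and no patient-level covariate can separate them from the intervention. The article's own call for caution must stay.

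**What to change.** In the Phase 3 Data analysis section:

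- State whether baseline scores means the outcome's own baseline.
- Prespecify baseline HbA1c as a covariate in the PAM model and all other non-HbA1c models, and baseline PAM in all non-PAM models.
- Confirm that medical treatment and height and weight are collected at Phase 3 baseline. If so, add treatment category and BMI to every model, with the categories fixed in advance.
- Add disease duration only if its value, and not just eligibility, is recorded.
- Optionally, add a propensity-score sensitivity analysis on the same variables. If overlap weights are used, say that they target a different population.
- Keep the cautious interpretation, and say explicitly that practice and nurse differences cannot be adjusted away.

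The cost is a wording change and about four degrees of freedom out of roughly 138 patients. HbA1c needs no new data. Treatment, BMI and duration would be small additions if they are not already in the Phase 3 data set. The stated sample size and power do not change. Fixing the list before outcome data are seen also prevents covariates being chosen by result.

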#### Sample size calculation

In GSD-like interventions, identification of a primary outcome differs from a traditional intervention study in that each individual participant (rather than the study director) determines the goals of the intervention. In essence, different patients have different primary outcomes. Nevertheless, for purposes of calculating power, a primary outcome must be identified. Since GSD is designed to increase patient involvement in goal selection and behaviour change, we have selected patient activation as the primary outcome. Therefore, change in patient activation is the primary end point as measured by the PAM scale total score. According to Steinsbekk,^55^ a detected difference in PAM score of six points (from 66.4 to 72.4) (SD 11.1) with 90% power and 5% significance level, the sample size must be 72 in each group. Given an expected dropout rate of 20%, we will include at least 172 patients in our study, 86 patients in each group.

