### Study overview

The study detailed in this protocol consists of three phases covering the first three stages of the MRC framework:^30^ (1) the modelling study, which has already been completed, (2) the feasibility study, which started in spring 2016 and is underway and (3) the evaluation study, which is planned to start in 2017. An overview of the different phases containing aims, methods and participants, respectively, is depicted in table 1.

**Table 1 BMJOPEN2016013026TB1:** Study overview

Phases	Aims	Methods	Participants
Phase 1. The modelling study	*Step 1*: Identifying areas to be changed from the original GSD. *Step 2*: Adapting the GSD to patients with T2DM, and for internet delivery.	Qualitative approaches with individual interviews in both steps, using qualitative content analysis. A resource group (12 in total) together with a group of user representatives (5 in total) identified adjustments applicable to adults with T2DM and for internet delivery.	*Step 1*: Eight patients with T2DM recruited from GPs. *Step 2*: Eight patients with T2DM recruited from GPs.
Phase 2. The feasibility study	Pretesting the adapted GSD intervention on the web and assessing its feasibility.	Quantitative: Pre–post design. Qualitative: Individual interviews at the end of the programme, using qualitative content analysis.	40 patients with T2DM who have participated in the web-based GSD adapted for T2DM will be recruited from GPs.
Phase 3. The evaluation study	Evaluating the effectiveness of a structured theory-driven web-based GSD intervention on self-management behaviours and HbA1c.	Quasi-experimental design with outcome assessments at baseline, end of programme and 6-month postprogramme.	A total of 172 patients with T2DM will be recruited from GPs (intervention group n=86, control group n=86).

GP, general practitioners; GSD, Guided Self-Determination; HbA1c, glycosylated haemoglobin; T2DM, type 2 diabetes.

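### Enrolling 86 per group leaves about 69 after the expected 20% dropout, short of the 72 the plan requires; power is about 89%, not 90%, a minor but real arithmetic slip

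*Protocol article*

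**What the plan says.** In Phase 3, Sample size calculation, the protocol article chooses one endpoint for the power calculation: "change in patient activation is the primary end point as measured by the PAM scale total score". The inputs are "a detected difference in PAM score of six points (from 66.4 to 72.4) (SD 11.1"), and the result is that "with 90% power and 5% significance level, the sample size must be 72 in each group".

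The next sentence allows for loss to follow-up: "Given an expected dropout rate of 20%, we will include at least 172 patients in our study, 86 patients in each group".

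Table 1 (Study overview) repeats the enrolment as a fixed figure: "A total of 172 patients with T2DM will be recruited from GPs (intervention group n=86, control group n=86").

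The article does not say which formula took 72 to 86. It also does not say whether the SD of 11.1 belongs to the PAM score or to its change, or whether the 5% level is one- or two-sided.

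**The concern.** A dropout rate is a fraction of the patients who enter. To finish with 72 per group after losing 20%, enrolment has to be 72 divided by 0.8. The stated 86 is lower than that and is close to 72 multiplied by 1.2, which adds 20% of the completers instead of allowing for the loss of 20% of those enrolled.

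At stake is whether the only power statement in the article, for the only endpoint chosen for that purpose, is true on its own inputs. The base calculation has no slack to absorb the shortfall, because 72 is the smallest whole number that reaches 90%.

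**Working it through.** **Inputs**, all from Sample size calculation: difference 6 points (66.4 to 72.4), SD 11.1, power 90%, significance level 5%, 72 required per group, dropout 20%, enrolment 86 per group (172 in total, repeated in Table 1).

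**Step 1. Reproduce the 72.** For two equal groups and a two-sided 5% test, by the normal approximation:

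n = 2 × (1.960 + 1.2816)² × 11.1² / 6² = 71.92, rounded up to 72.

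This matches the plan. A one-sided test would give 59, so the plan evidently used a two-sided level. The exact calculation by noncentral t needs 73 per group. The base figure is therefore sound, and the problem lies only in the dropout step.

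**Step 2. Find where 86 comes from.**
- 72 × 1.2 = 86.4, and 144 × 1.2 = 172.8. These match 86 and 172 if rounded down.
- 72 / (1 − 0.20) = 90, and 144 / 0.8 = 180. These do not match.

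The multiplication by 1.2 is inferred from the result; the article does not print it.

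**Step 3. Apply the stated dropout to the stated enrolment.**
- 86 × 0.8 = 68.8 per group, about 69 (172 × 0.8 = 137.6 in total, against 144 required).
- Shortfall: 72 − 68.8 = 3.2 completers per group.
- Largest dropout that still leaves 72: 1 − 72/86 = 16.3%.

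**Step 4. Power with what remains.** By the normal approximation, power = Φ( (6/11.1) × √(n/2) − 1.960 ).
- At n = 68.8: (6/11.1) × √34.4 = 3.170; 3.170 − 1.960 = 1.210; power 88.7%.
- At n = 72: (6/11.1) × √36 = 3.243; 3.243 − 1.960 = 1.283; power 90.0%.

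| Completers per group | Normal approximation | Noncentral t |
|---|---|---|
| 68.8 | 88.7% | 88.3% |
| 72 | 90.0% | 89.6% |

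Within either column the loss is about 1.3 points. The difference detectable with 90% power at 68.8 per group is 3.2415 × 11.1 × √(2/68.8) = 6.13 points by the normal approximation, against the planned 6.

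**Step 5. Enrolment that would be consistent.** 72 / 0.8 = 90 per group, 180 in total. That is 4 more per group and 8 more in total than planned. Check: 90 × 0.8 = 72.

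**The case against.** **The analysis may recover the power.** This is the strongest argument. The Phase 3 Data analysis section plans regression with baseline score, age and gender as covariates, whereas the sample size formula is an unadjusted comparison of two means. Suppose 11.1 is the SD of the PAM score and the baseline-outcome correlation is ρ, neither of which the article states. Adjustment then multiplies the variance by 1 − ρ². Restoring 90% at 68.8 per group by the normal approximation needs 1 − ρ² = 68.8/71.92 = 0.957, that is, ρ of about 0.21. At ρ = 0.3 power would be about 91%. These are modest correlations, so the point stands as a reason not to worry much about the final power. It does not rescue the stated arithmetic, because the calculation claims no such gain and gives no correlation. If 11.1 is the SD of change, this argument does not carry over as it stands.

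**The total is a minimum.** The Sample size section sets 172 as a floor, so enrolling 180 would not breach that wording. But the floor itself is too low for the stated requirement, and both the per-group figure and Table 1 are given without the qualifier.

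**The loss is trivial.** It is small, and the plan already urges caution because allocation is not random. This bears on how serious the point is, not on whether the sentence is correct.

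**It is a condensed article.** Condensation explains missing detail. Here all the figures are printed, and they disagree.

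**Conclusion.** The point holds as a minor correction. On the plan's own inputs, 86 per group with 20% dropout does not leave the 72 per group that the plan says are needed. The shortfall is about 3 completers per group, and power is about 89% instead of 90% (normal approximation), or 88.3% instead of 89.6% (noncentral t). This rests on a two-sided 5% test, equal groups, the same 20% dropout in each group, analysis of completers and no gain from covariates.

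The documents do not support three stronger readings that a reader might infer:

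- *That power falls from 90% to 88.3%.* This sets a noncentral t figure against a normal-approximation figure. By noncentral t, 72 per group itself gives only 89.6%, so the like-for-like loss is about 1.3 points.
- *That the plan is shown to have multiplied by 1.2.* This is the likely explanation, but the formula is not given. The finding does not depend on it, since 86 × 0.8 falls below 72 however 86 was reached.
- *That the study is materially underpowered or must recruit more.* A loss of this size, which baseline adjustment might offset, does not by itself call for a change of design. Whether clustering within practices affects power is a separate question and adds no weight to this one.

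**What to change.** Correct the dropout sentence in Sample size calculation in one of two ways, leaving enrolment as it is:

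- State that 86 per group leaves about 69 per group after 20% dropout, giving about 89% power (normal approximation; 88% by exact t) for a 6-point difference with SD 11.1.
- Or keep the 90% figure and state that it holds (by the normal approximation) only if dropout is at most about 16%.

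Either costs one sentence; the first also means reporting a slightly less favourable power figure. Table 1 needs no change.

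If the sponsor prefers to keep 90% power at 20% dropout, the consistent enrolment is 90 per group (180 in total). That costs 8 more patients, and the Sample size section and Table 1 should then both be updated. This is an option, not a requirement of the correction.
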